#### Sociodemographic factors

Sociodemographic information includes age, sex, pre-admission setting (home, family home, long-term care, other hospital wards), and assistance needs from home.

#### Comprehensive geriatric assessment

Functional status will be assessed using the validated Basic Activities of Daily Living (BADL) and Instrumental Activities of Daily Living (IADL) scales [14, 15]. The presence of cognitive deficits will be evaluated using the Short Portable Mental Status Questionnaire (SPMSQ) [16].

Chronic medical illness burden will be quantified using the Cumulative Illness Rating Scale (CIRS) [17]. Delirium screening will be performed using the 4AT screening tool [18].

Nutritional status and sarcopenia screening will be evaluated using the Mini Nutritional Assessment Short Form (MNA-SF) and SARC-F [19, 20]. Anthropometric measurements, including body weight, height, and calf and arm circumferences, will be recorded for each participant. Pressure sore risk will be determined using the Exton-Smith Scale (ESS) [21]. Depressive symptoms will be assessed using the Geriatric Depression Scale (GDS) [22], and physical performance through handgrip strength and 4-m walking speed, only for those who are able to walk independently or with walking aids.

Furthermore, we will collect data on the patient’s medication history, including medications used chronically before admission and those prescribed at discharge. Information on vaccination history, alcohol consumption, and smoking status will also be obtained.

#### Infectious disease

The presence of infectious diseases will be determined through routine clinical, radiological, biochemical, and microbiological analyses and coded according to the following ICD-9 codes: 001–139 (Infectious diseases); 460–466 (Acute respiratory infections); 480–487 (Pneumonia, flu disease); 320–326 (Nervous system infections); 540–543 (Appendicitis); 590, 595.0, 595.4, 599.0, 597 (Urinary system infections); 601, 604 (Prostatitis, orchitis, and epididymitis); 616, 574.0, 571.1 (Gynecological system infections); 572.0, 573.1, 573.2 (Acute hepatitis, liver abscess); 575–576.1 (Cholecystitis, cholangitis).

Each documented infectious disease will be characterized by its etiology (if known), and the prescribed antimicrobial therapy will be recorded, including the specific drug and duration. Any concomitant or subsequent infectious diseases arising during hospitalization will be similarly documented. In addition, the Sequential Organ Failure Assessment (SOFA) score will be calculated for each patient to assess infections’ severity [23].

#### Frailty status

Frailty will be evaluated using the Primary Care – Frailty Index (PC-FI) [24] and the Clinical Frailty Scale (CFS) [25]. The PC-FI is a reliable and validated tool developed in Italian older adults to assess frailty in the primary care setting. It was chosen considering that both the pre-admission and post-discharge assessment will involve older adults in primary care. In particular, pre-admission frailty status will be derived retrospectively to reflect the status of participants two weeks before hospital admission.

Frailty assessment will be repeated 48 h before hospital discharge and at a 3-month follow-up.

#### Genetic and epigenetic analyses

At Time 1 and Time 3 (only for a subsample of participants), blood samples will be collected and processed for plasma and blood cell stocking for DNA extraction.

DNA extraction from whole blood will be performed by Automated Genomic DNA Purification EZ1 XL machine (QIAGEN).

Global DNA methylation assessment will be performed by “highly quantitative pyrosequencing” technique as genome-wide DNA methylation levels and as gene promoter associated CpG islands utilizing selected age-related methylation marker loci and at LINE-1, Alu, Sat-alpha repetitive elements (as a surrogate for global genome methylation) as previously described [26–28]. Results will be also confirmed by internal Illumina Infinium 450 k beadchip array.

Leukocyte Telomere Length (LTL) will be determined using quantitative real-time PCR (QuantStudio™ 3 System; Applied Biosystems) according to the method of Cawthon [29], the 36B4 will be used as a single copy gene reference (SCR), and the ratio Telomere/36B4 (T/S) will be estimated as indicator of LTL [2 − ∆Ct (△Ct = Ct TL − Ct 36B4)].

#### Biochemical analyses

We will monitor the plasma levels of circulating markers associated with key biological processes related to frailty, such as (1) pro-inflammatory state (including but not limited to TNF-a, IL6, CRP, TRAIL/OPG, CXCL10, MCP-1); (2) metabolic/endocrine imbalance (including but not limited to Cystatin-C, IGF-1); (3) functional brain modifications (including but not limited to BDNF, CSF); (4) oxidative stress (including but not limited to PON-1, Homocysteine).

Analysis will be performed using Luminex Technology, a platform allowing the simultaneous detection and quantification of multiple secreted proteins, including cytokines, chemokines, and growth factors. Customized panels will be generated with targets of interest.

Ox-stress markers will be analyzed using fluorimetric/ELISA assays.

Selected inflammatory markers will be monitored by ProQuantum High-Sensitivity immunoassays (TermoFisher, Waltham, MA USA) to achieve a highly sensitive assay to detect lower protein levels.

### Statistical analysis

The baseline characteristics of the study participants will be described using count and proportion for the categorical variables and mean and standard deviation, or median and interquartile ranges, for the quantitative variables, according to their distribution. These characteristics will be compared between participants by type of infection and the presence of systemic inflammatory response through the ANOVA, Student t-test, Kruskal Wallis test, or Chi-squared test, as appropriate.

The intra-individual change in FI between the pre-admission status and the patient’s condition at hospital discharge will be evaluated through the Student t-test for paired samples and then with linear mixed models. The latter analysis will be set with a random intercept and slope and adjusted for potential confounders in the association between infectious diseases and frailty changes, e.g., sociodemographic information, study center, comorbidities, length of hospital stay, and in-hospital clinical events (unrelated to the infection). The mean adjusted change in FI between pre-admission status and hospital discharge will be expressed as ß coefficient and 95% confidence interval (95% CI). Moreover, we will test whether the presence of systemic inflammation will modify the average intra-hospital change in FI. As secondary analyses, we will investigate which infection-related characteristics will be associated with higher in-hospital mortality (through the Kaplan-Mayer method and Cox regression analysis), longer hospital stay (with linear regressions), and discharge setting (with multinomial logistic regression).

The impact of infectious diseases (distinguished by number, site and severity) on frailty changes will be analyzed with linear mixed models, considering the beta coefficients (95% CI) for the interaction infection*time. Additional analyses will be performed to test whether sociodemographic, functional, clinical, and genetic/epigenetic factors interact with infectious diseases to influence the course of frailty over time.

The patterns of global DNA methylation will be assessed in duplicate for each sample and expressed in percentage as the mean obtained by the two evaluations and considered valuable with a discrepancy < 2%. Methylation percentages will be stratified into quartiles, and the combined middle two quartiles will be used as the reference category to identify potential correlations at the top or bottom of the distribution with the clinical phenotypes. As a measure of the relative Telomere length, the ratio of the telomere repeat copy number to the number of single-copy genes (T/S ratio) will be determined by quantitative PCR using the single-copy gene 36B4 for reference and a standard curve. Quality controls and assay validation tests will be assessed by official commercially recognized standards (Qiagen, LifeTechnology). The association of global DNA methylation pattern and telomere length with the frailty trajectories will be evaluated through a linear mixed model, adjusted for potential confounders. Appropriate subgroup and interaction analyses will be performed to explore the possible modifying effects by sex, the presence of the most prevalent clinical conditions, and infection-related factors (i.e. number, site, and severity of infections) on the studied associations.

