The specific aims of the study will be: a) to assess the impact of infections—both with and without systemic inflammatory response—on frailty profiles from pre-admission to hospital discharge in older patients with no to mild pre-admission frailty (*primary aim*); b) to examine the link between changes in frailty and genetic/epigenetic markers, such as global DNA methylation and telomere length, exploring whether these biomarkers can predict the course of in-hospital and post-discharge frailty; c) to evaluate the trend of circulating inflammatory and aging-related biomarkers in modulating the impact of infections on frailty progression; and d) to assess the impact of infections on frailty trajectories over a three-month follow-up after discharge, and the modifying role of sociodemographic, clinical and (epi)genetic factors.

While previous research has linked hospitalizations to a decline in physical and cognitive health, leading to frailty in older patients, limited evidence exists on how infections specifically drive these changes. We hypothesize that patients experiencing a higher number and severity of acute infections, especially those with underlying systemic inflammation, may show a steeper functional decline during and after hospitalization. Additionally, we expect that genetic, epigenetic, and clinical factors—such as older age, multimorbidity, polypharmacy, specific DNA methylation and telomere length patterns—may modify the progression of frailty in response to infections.

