First, the study will quantify the impact of infections on the change in individuals’ frailty status from pre-admission to hospital discharge. Evidence from the SARS-CoV-2 pandemic suggests that infectious diseases can substantially promote frailty development even beyond 3 months of acute illness [7, 8]. However, data on how the most common types of infection, their severity, the occurrence of multiple infectious diseases, and their related level of systemic inflammation may influence the progression of frailty in older adults are lacking. Furthermore, there is some heterogeneity in the definitions of frailty adopted across various studies. Second, the project will explore the interaction between infections and in-hospital frailty status in influencing adverse endpoints, such as in-hospital mortality, length of hospital stay, and discharge destination. For instance, sepsis in frail patients has been shown to worsen mortality compared to non-frail patients [31], and other infections such as pneumonia, COVID-19, or influenza may have similar detrimental impacts [32–34]. Additionally, frailty is linked to a higher risk of urinary tract infections [35]. Third, the project will assess whether global DNA methylation and telomere length patterns at hospital admission are predictors of in-hospital and post-discharge frailty trajectories. In the literature, these epigenomic and genomic markers have been linked to cellular senescence and aging [36]. For example, shorter LTL have been associated with increased risk of infections, various malignant tumors (esophageal cancer, lymphoid and myeloid leukemia), and mortality from cardiovascular, respiratory, digestive, and musculoskeletal diseases and COVID-19 [11]. However, the role of these genomic markers in predicting frailty or functional changes has not been fully investigated [13]. This project will allow us to explore whether DNA methylation and telomere length variations are involved in the pathogenetic processes leading to frailty, especially following an infection. Notably, epigenetic modifications and telomere attrition (dynamic epigenomics) are sensitive to exogenous and endogenous stressors, which strongly relates to an individual’s baseline epigenome and their personal response to stressors, thus accounting for the relationship between epigenomic patterning and developmental trajectories or disease [37]. Although a 3-month period may be a short time interval to detect changes in LTL, we cannot rule a negative impact of infectious diseases and inflammatory processes on this aspect in vulnerable individuals, such as older inpatients. Moreover, blood cells composition of the included participants is expected to change between in-hospital and post-discharge assessments, and this issue may further influence LTL.

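### In-hospital deaths have no discharge Frailty Index, so the planned infection contrasts describe survivors and are probably, though not certainly, attenuated

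*Protocol article*

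**What the plan says.** All references are to the protocol article.

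- **Measurement (Frailty status).** "Frailty assessment will be repeated 48 h before hospital discharge and at a 3-month follow-up". The pre-admission value is reconstructed at admission and refers to two weeks earlier.
- **Primary change (Statistical analysis).** The within-patient FI change up to discharge "will be evaluated through the Student t-test for paired samples and then with linear mixed models". The section also tests whether systemic inflammation modifies this change.
- **Infection contrasts (Statistical analysis).** "The impact of infectious diseases (distinguished by number, site and severity) on frailty changes will be analyzed with linear mixed models", read from the infection-by-time interaction.
- **Death (Statistical analysis).** As a separate secondary analysis by Kaplan-Meier and Cox methods, "we will investigate which infection-related characteristics will be associated with higher in-hospital mortality".
- **Hypothesis (Background).** "patients experiencing a higher number and severity of acute infections, especially those with underlying systemic inflammation, may show a steeper functional decline".
- **Related promise (Discussion).** "the project will explore the interaction between infections and in-hospital frailty status in influencing adverse endpoints, such as in-hospital mortality".

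The article does not say how patients who die before discharge enter the FI analysis.

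**The concern.** The primary quantity needs an FI that exists only for patients who come close to leaving hospital alive. The article itself anticipates that death varies with the infection characteristics whose effect on FI it wants to estimate, and it hypothesises that these characteristics also drive decline. If both hold, patients go missing in relation to exposure and outcome together.

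The mixed model looks like the remedy for incomplete pairs, but for this contrast it is a weak one. A patient who dies in hospital contributes only the pre-admission value. A likelihood-based model can therefore recover only the part of that patient's change that pre-admission FI and covariates predict. It cannot recover a link between death and the in-hospital decline itself.

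At stake is the interpretation of the severity, number and systemic-inflammation contrasts. The aim is worded for older inpatients with infection, while the estimate describes those who survived the stay. A lethal type of infection could look mild for frailty because the patients it harmed most are not in the comparison.

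**Working it through.** **Inputs.** From the article: a difference of 0.03 FI points, 340 patients, alpha 0.05 and power 80% (Sample size calculations). The article gives no in-hospital mortality, no SD of FI change and no association between decline and death, so these are assumptions.

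**The plan's own figure.** 340 cannot be reproduced without an SD. Solved backwards for a paired change with two-sided alpha: SD = 0.03 × √340 / (1.960 + 0.842) = 0.197. I use 0.10 as the main assumed SD and 0.197 as an alternative.

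**Step 1: size under a simple selection model.** Let FI change and liability to death be bivariate normal with correlation ρ, and let a proportion p die. The mean change among survivors shifts by −ρ × SD × φ(z)/(1 − p), where z is the upper-p normal quantile.

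- p = 5%: φ(1.645)/0.95 = 0.1031/0.95 = 0.1086
- p = 15%: φ(1.036)/0.85 = 0.2332/0.85 = 0.2743
- p = 20%: φ(0.842)/0.80 = 0.2800/0.80 = 0.3500

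The severe-minus-mild contrast moves by the difference in shifts:

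| SD | ρ | Deaths, mild vs severe | Shift in contrast | True 0.030 appears as |
|---|---|---|---|---|
| 0.10 | 0.5 | 5% vs 20% | −0.5 × 0.10 × (0.3500 − 0.1086) = −0.0121 | 0.018 |
| 0.10 | 0.3 | 5% vs 15% | −0.3 × 0.10 × (0.2743 − 0.1086) = −0.0050 | 0.025 |
| 0.197 | 0.3 | 5% vs 15% | −0.3 × 0.197 × (0.2743 − 0.1086) = −0.0098 | 0.020 |

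**Step 2: does the mixed model help, and is the direction fixed?** A simulation with 1,000,000 patients per scenario used a mean change of 0.05 in severe and 0.02 in non-severe infection (true difference 0.030). It compared survivors only with a likelihood-equivalent model conditioning on pre-admission FI. Deaths were 15% severe and 5% non-severe unless stated.

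| Pattern of death | Contrast, SD 0.10 | Contrast, SD 0.197 |
|---|---|---|
| Unrelated to FI change | 0.030 | 0.030 |
| Odds double per SD of worsening, both groups | 0.024 | 0.017 |
| Odds triple per SD of worsening, both groups | 0.021 | 0.012 |
| Odds double, but deaths 10% in both groups | 0.030 | 0.030 |
| Odds triple in the non-severe group only | 0.035 | 0.041 |

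Death depending only on pre-admission FI (run at SD 0.197) also left the contrast at 0.030. The mixed-model estimate matched the survivors-only estimate in every scenario. Pre-admission FI was simulated independently of the change; if it predicted the change, the model would recover that predictable part and no more.

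**Step 3: the overall change.** With 10% deaths in both groups and doubled odds, the contrast is unbiased, but the mean change falls from 0.035 to 0.029 (SD 0.10) or 0.022 (SD 0.197). This is the quantity that the paired t-test estimates.

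**The case against.** The strongest reply is that handling of deaths and sensitivity analyses commonly belongs in an analysis plan that is not shown, and that a change up to discharge is naturally a quantity in patients who reach discharge. Mortality by infection characteristics is analysed separately, so a reader could set the two side by side. Excluding patients with a life expectancy under 3 months also limits deaths. Much of this stands: a survivor estimate is legitimate if it is named as such, and the article nowhere states a missing-at-random assumption, which is a property of the model it names. What does not fall away is that the article fixes measurement time, contrast and estimator, and these do not answer the question for all inpatients. The exclusion does not remove deaths from the acute infection.

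Four stronger readings are tempting but unsupported:

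- **That severity effects are certainly understated.** The second table shows null and reversed patterns. There is also no true FI after death, so understatement presupposes a hypothetical or composite target that the article does not adopt.
- **That the paired t-test biases the severity effect.** It estimates the overall change. The severity statement applies only to the mixed-model interaction.
- **That the 3-month trajectories suffer equally.** Patients who die after discharge have an observed discharge FI on which the model conditions. Only the in-hospital deaths carry the same problem forward.
- **That the interaction announced in the Discussion cannot be computed.** An FI taken just before discharge cannot predict in-hospital death, but in-hospital frailty status is undefined there. It may mean the rating made at admission, which exists for everyone.

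**Conclusion.** The point holds in a limited form. The paired t-test describes change in patients discharged alive. The mixed-model contrasts by infection characteristics and systemic inflammation rest on those survivors or on implicit projection for the dead. For the pre-admission-to-discharge change, the named model cannot repair a link between death and in-hospital decline.

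Attenuation is probable if two conditions hold: deaths are more frequent in severe infection, and they fall on patients with steeper decline to a similar degree in each group. Both fit the article's own expectations, but neither is given as a figure. Under the main assumed inputs, a true 0.030 appears as about 0.018 to 0.025, a loss of 17% to 40% (0.0050/0.030 and 0.0121/0.030). These percentages illustrate scale and are not estimates for this study. The matter deserves correction before analysis but does not invalidate the design.

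**What to change.** 1. State that the FI-change estimate applies to patients discharged alive, and report it beside in-hospital mortality for the same groups.
2. For the severity, number and systemic-inflammation contrasts from pre-admission to discharge, pre-specify one sensitivity analysis: either in-hospital death ranked worse than any FI change, or a joint FI-survival model. Interpret it together with the survivor estimate.
3. Extend this to 3 months only if vital status after discharge is recorded. The article describes no such collection.
4. For the interaction of infection with frailty on in-hospital mortality, specify pre-admission FI or CFS, which is available for all participants.

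The cost is a little extra analysis. The in-hospital death data are already needed for the Cox regression. The drawback of the composite is that its result is in ranks and not in FI points.

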## Background

Frailty, a geriatric syndrome characterized by reduced biological reserves and increased vulnerability to stressors, represents a cornerstone of geriatric clinical practice and research. As the global population ages, this syndrome is expected to constitute an increasingly pressing public health problem. It is associated with several adverse outcomes, including acute and chronic conditions, disability, cognitive decline, and mortality [1, 2].

Frailty exacerbates age-related changes in the immune system and chronic inflammation [3], presumably increasing the individual vulnerability to infections. In turn, infections can trigger inflammatory responses and aggravate the detrimental effects of hospitalization on the individual’s resilience and functional status [4]. Previous studies have shown a link between frailty at hospital admission and adverse outcomes in patients with infectious diseases, including an increased risk of hospital readmission and mortality [5] and poorer medium-term functional trajectories [6]. However, the intricate relationship between frailty and acute infections remains poorly understood, as does the impact of acute infections on this geriatric syndrome.

To date, research focuses mainly on COVID-19 and shows that infection significantly worsens frailty, particularly in hospitalized patients [7] and those with pre-existing frailty [8]. Moreover, studies investigating changes in frailty during hospitalization have generally assessed frailty only at admission, neglecting the pre-admission status and often overlooking the potential impact of infectious diseases [9, 10].

An interesting aspect to consider in the context of the interplay between frailty and infections is the role of genetic and epigenetic biomarkers. Emerging research points to the potential involvement of factors, such as global DNA methylation and telomere length, in the development and progression of frailty [11–13]. However, further studies are necessary to gain a deeper understanding of their roles and potential clinical implications.

The INFRAGEN prospective multicenter study aims to evaluate the impact of infections on changes to frailty in hospitalized older patients, focusing on clinical, biochemical, genetic, and epigenetic markers at hospital admission. Moreover, the study will examine whether changes in frailty over three months are linked to epigenomic DNA modifications in a subgroup of patients.

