## Methods/design

### Study design and participants

The INFRAGEN study is a prospective, observational multicenter study involving the Acute Geriatric Units of four Italian centers: S. Anna University Hospital in Ferrara (Emilia-Romagna region, Italy), Padua University Hospital (Veneto region, Italy), IRCCS Foundation San Gerardo dei Tintori in Monza (Lombardy region, Italy), and Federico II University Hospital (Campania region, Italy).

Participants will be selected based on the following criteria: age ≥ 70 years, non-frailty or mild frailty status before admission (CFS < 6), and confirmed diagnosis of acute infectious diseases at the time of hospital admission or during the hospital stay, according to specific ICD-9 codes, with or without a systemic inflammatory response.

Terminally ill patients with an estimated life expectancy of less than 3 months, those with moderate to severe frailty, and individuals who do not wish to participate in the study or complete follow-up assessments will be excluded.

Written informed consent will be obtained from all participants.

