### Sample size calculations

Based on previous reports on the topic [10], we estimated that a total sample of at least 340 older adults with acute infections would be sufficient to detect a minimal clinically significant difference in Frailty Index (FI) of at least 0.03 points from the pre-admission status to hospital discharge, with an alpha of 0.05, and a power of 80%.

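### Every participant is infected, so the powered pre-admission-to-discharge FI change cannot measure the impact of infections; only the planned within-cohort contrasts bear on it, and the power statement does not cover them

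*Protocol article*

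**What the plan says.** - **Who is enrolled.** Eligibility requires a "confirmed diagnosis of acute infectious diseases at the time of hospital admission or during the hospital stay" (Protocol article, Study design and participants). No uninfected group is described.
- **What is powered.** Sample size calculations says of the cohort that "a total sample of at least 340 older adults with acute infections would be sufficient to detect" the target effect. That effect is defined as a "difference in Frailty Index (FI) of at least 0.03 points from the pre-admission status to hospital discharge". Alpha is 0.05 and power is 80%. The section gives no SD and does not say whether alpha is one- or two-sided.
- **What is promised.** The primary aim, at the end of the Background, is the impact of infections, with or without a systemic inflammatory response, on frailty up to discharge. The Discussion repeats this: "First, the study will quantify the impact of infections on the change in" frailty over that interval.
- **How the change is analysed.** In Statistical analysis, the intra-individual FI change "will be evaluated through the Student t-test for paired samples and then with linear mixed models". The model is adjusted for centre, comorbidities, length of stay and in-hospital events, among others, and reports an adjusted mean change.
- **What else is planned.** The same section will test whether systemic inflammation modifies the in-hospital FI change. It also plans infection-by-time interactions for number, site and severity of infection.
- **How the starting point is measured.** Under Frailty status, the pre-admission state (two weeks before admission) is derived retrospectively.

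**The concern.** An effect of infection is a contrast between different levels of infection. The paired difference and the adjusted time coefficient contain no such contrast, because everybody in them is infected. They measure everything that happened to FI between the recalled pre-admission state and discharge.

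The aims text itself supplies a rival explanation: it notes that hospitalisations have been linked to physical and cognitive decline, and that evidence on the specific part played by infections is limited. A pre/post mean in infected inpatients does not fill that gap. At stake is the headline conclusion. A clear FI rise could be reported as the impact of infections when the analysis cannot attribute it to them, and the contrasts that do vary infection carry no power statement.

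**Working it through.** **1. What the model can identify.** Write the FI model with terms for time, infection and infection × time. If infection equals 1 for every patient, the time and infection × time columns are identical, so only the sum of the two coefficients can be estimated. Covariate adjustment changes the patient mix to which that sum refers. It does not supply an unexposed patient. The paired t-test estimates the same sum without adjustment.

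**2. What that sum contains.** It includes infection, the stay itself, any other acute illness, treatment, and any error from scoring the pre-admission state in retrospect. Infections arising during the stay also qualify, so for those patients the interval includes hospital time before infection.

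**3. The plan's own figure.** Inputs from Sample size calculations: n = 340, difference 0.03, alpha 0.05 (two-sided assumed), power 80%. The multiplier is 1.960 + 0.8416 = 2.8016. With no SD stated, 340 can only be solved backwards:

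- Paired: SD of change = 0.03 × √340 / 2.8016 = 0.197.
- Two groups of 170: SD = 0.03 / (2.8016 × √(2/170)) = 0.099.

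Both are possible readings. The figure is neither confirmed nor refuted.

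**4. The paired test when infection adds nothing.** Suppose the stay alone raises FI by h. The values of h and the SDs are assumptions for illustration. The probability of rejection with 340 pairs, from the noncentral t distribution, is:

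| h | SD 0.197 | SD 0.10 |
|---|---|---|
| 0.02 | 46% | 96% |
| 0.03 | 80% | >99.9% |

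A larger sample raises these probabilities and does nothing to separate the causes.

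**5. A contrast that does vary infection.** Take FI change with versus without systemic inflammation, with an assumed 170/170 split. The detectable difference at 80% power is 2.8016 × SD × √(2/170). Power for a difference of 0.03 is Φ(0.03 / (SD × √(2/170)) − 1.960).

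| Assumed SD of change | Detectable difference | Power for 0.03 |
|---|---|---|
| 0.08 | 0.024 | 93% |
| 0.10 | 0.030 | 79% |
| 0.12 | 0.037 | 64% |
| 0.15 | 0.046 | 45% |
| 0.197 | 0.060 | 29% |

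An uneven split is less favourable. With an assumed 85/255, √(1/85 + 1/255) = 0.125 replaces √(2/170) = 0.108. The detectable difference becomes 0.035 at SD 0.10 and 0.069 at SD 0.197.

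**The case against.** The strongest reply is that the impact of infections does not rest on the pre/post mean alone. Statistical analysis uses that very idea for the infection-by-time models. The primary aim mentions infections with and without systemic inflammation, the stated hypothesis is a gradient in number and severity, and the Discussion goes on to type, severity and multiplicity. The inflammation test appears before the secondary analyses are introduced, and the section never labels the paired t-test primary; that status is inferred from the aim and the sample size. All of this stands. It means the plan already holds the material for a remedy. It does not make the pre/post mean an infection effect, and the power statement still attaches to that mean.

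Several stronger readings are tempting but not supported:

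- *A significant pre/post result is to be expected even without any infection effect.* The documents give no size for the change due to the stay, so the figures in step 4 are conditional. What is supported is that the test cannot tell the causes apart.
- *The 0.03 was taken from studies that ignored infection.* The Background does describe the studies it cites, including reference 10, as "often overlooking the potential impact of infectious diseases [9, 10"]. The sample size paragraph says only that its estimate builds on reference 10, and presents 0.03 as a minimal clinically significant difference. What that report supplied cannot be seen.
- *Hospitalisation alone is stated to cause decline.* The text reports a link and does not isolate hospitalisation.
- *Selection at CFS < 6 produces regression to the mean.* This is plausible, but selection is on the CFS and the outcome is the FI, and nothing allows its size to be estimated.
- *The inflammation contrast has only 29% power.* This holds only on the paired reading of 340 with an even split. On the two-group reading (SD 0.099) the same contrast has 80%.

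The absence of an SD or an attrition allowance from a condensed article is not itself criticised.

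**Conclusion.** The point holds in this form: the paired t-test and the adjusted mean FI change estimate total change over a hospital stay with infection. They do not support the statements in the aims and the Discussion that the impact of infections will be assessed or quantified. This follows from the eligibility criteria and needs no assumption about SDs or group sizes. The limitations in the Discussion cover recruitment, ethnic homogeneity and Italian-only units, but not this.

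The planned contrasts do inform on infection, as a gradient among infected patients, and are outside the power statement. Their detectable difference runs from about 0.03 (SD of change about 0.10) to about 0.06 (SD about 0.197), assuming a two-sided 0.05 test, 80% power and a 170/170 split. A reader should not infer that 340 is miscalculated, or that the plan has no analysis bearing on infection. Neither follows from the document.

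**What to change.** 1. In the primary aim and the Discussion, describe the pre/post mean as FI change among older patients hospitalised with infection, not to be interpreted as the effect of infection. Add the missing uninfected comparator to the limitations.
2. Name one contrast already planned, for example systemic inflammatory response × time on FI at discharge, as the analysis on which any statement about the impact of infection rests. Present it as a gradient among infected patients.
3. In Sample size calculations, say that 340 and 80% power refer to the within-person change only. Quote the detectable difference for the contrast in (2) under a stated SD of change and group split.

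The cost is wording and one short calculation, with no extra patients or assessments. The downside is a more modest claim and possibly a less favourable quoted detectable difference.
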